### Acceptability

Acceptability measures incorporate participant feedback or satisfaction survey (see Multimedia Appendix 3). During study participation, each participant will be asked at least once if they wish to provide feedback on their experience of attaching or wearing the biosensor during injecting drug use. Participants may complete the feedback questionnaire more than once to record fluctuating levels of acceptability. For any feedback provided, the site will collate responses and provide them as an anonymized table listing (see Multimedia Appendix 3). There will also be a subset of participants who will be interviewed and surveyed in more depth.

### Participant Timeline and Study Visits

The process of the investigation is more clearly understood through an examination of the schedule of events (visits 1 and then subsequent visits).

### Baseline Procedures

#### Overview

After the participant has consented, completion of participant’s basic, baseline (eg, demographics and drug use characteristics) questionnaire will be conducted using a stand-alone data collection tool using an electronic tablet. Each participant’s height and weight will be recorded at the site at baseline and changes in their height and weight will be recorded every 4 weeks.

The following schedule of events will be followed for visit 1 and then visit 2 (until withdrawal or final self-injecting event).

#### Visit 1 Procedures (Performed by Site Research Personnel)

Initially, research personnel will confirm the injection of opioids (either alone or in combination with other drugs) and then provide instructions on the use and wearing of the biosensor (Table 1). The biosensor will then be issued to the participant and the biosensor number will be recorded with the participant ID number. The researcher will verify that the biosensor has been correctly attached to the chest wall and provide further guidance to the participant, as required.

**Table 1 table1:** Visit 1 (baseline and first study–specific self-injecting visit).

	Enrollment or baseline	Prior to injecting event	Acute or overdose event^a^	Postinjecting event	Early withdrawal^b^
Informed consent^c^	✓				
Eligibility criteria	✓				
Complete baseline questionnaire	✓				
Instructions (use of biosensor)		✓			
Issue chest sensor		✓			
Attach to chest wall		✓			
Record of event^d^			✓		
Adverse events		✓	✓	✓	✓
Return of biosensor				✓	
Early withdrawal form					✓

^a^If a self-injecting event occurred without the need for intervention the event should be recorded to reference the time of the device was attached and returned and that no interventions were required.

^b^If participant withdraws after providing consent and prior to any use of the sensor.

^c^Consent and eligibility review, performed at a time most suitable to site personnel and participant during their visit (Multimedia Appendix 4).

^d^Event start time, event stop time, assessment of event, and event outcome, if an applicable acute event occurs.

Research personnel will record basic information (day or time and drug reported for injection) for each participant’s SIF attendance. Site research personnel will record the time of self-injecting by monitoring participants from a distance and estimating the time of drug injection (this may include multiple injections within a single episode). If this is not possible to record, the site personnel will document that it could not be collected. Site research personnel will also record event interventions for an acute or overdose event (as applicable), including start time, end time, event assessment or level of intervention, clinicians’ unique ID, and overdose criteria. A record of “no acute event” will also be maintained if the self-injecting visit occurred without any requirement for site personnel intervention. Any adverse events will also be recorded and, if necessary, an early withdrawal form will be completed if the participant did not progress to use the biosensor at visit 1 and declined further participation.

#### Visit 2 to Withdrawal or Final Self-Injecting Visit (Performed by Site Research Personnel)

At visit 2 and subsequent visits until withdrawal or final self-injecting visit, research personnel will verify that the informed consent remains valid for the participant to continue on the study (Table 2). They will also confirm the injection of opioids (either alone or in combination with other drugs) and provide a reminder instruction on the use and wear of the biosensor. They will then issue the biosensor to the participant and record the biosensor number used with the participant ID. They will verify that the biosensor has been attached to the chest wall correctly and provide further guidance to the participant as required.

**Table 2 table2:** Visit 2 to final self-injecting visit.

			Prior to injecting event		Acute or overdose^a,b^ event		Postinjecting event		Withdrawal^c^
Verify informed consent remains valid			✓						
Instructions (use of sensor; as required)			✓						
Issue chest biosensor			✓						
Attach to chest wall			✓						
Record of event^d^					✓				
Adverse events					✓		✓		✓
Return of biosensor							✓		
**User experience survey (during enrollment period, prior to withdrawal, or final self-injecting visit**									
	Withdrawal form^c^							✓	

^a^If a self-injecting event occurred without any need for intervention the event should be recorded to reference the time the device was attached and returned and that no interventions were required.

^b^If a self-injecting event occurred without the need for intervention the event should be recorded to reference the time of the device was attached and returned and that no interventions were required.

^c^For all withdrawals from visit 2 onwards.

^d^Event start time, event stop time, assessment of event, and event outcome, if an applicable acute event occurs.

Site research personnel will record basic information (day or time and drug reported for injection) for each participant’s SIF attendance and will record the time of self-injecting by monitoring the participant from a distance and estimating the time of drug injection (may include multiple injections within a single episode). If this is not possible to record, the site personnel will document that it could not be collected. Site research personnel will also record event interventions for an acute or overdose event (as applicable) including start time, end time, event assessment or level of intervention, clinicians’ unique ID, and overdose criteria. A record of “no acute event” will also be maintained if the self-injecting visit occurred without any requirement for site personnel intervention. Any adverse events will also be recorded and, if necessary, a withdrawal form will be completed if the participant did not progress to use the biosensor and declined further participation.

### Example Study Schedule

The number of visits and injection events per participant will differ. The following range of frequency of attendees at the SIF may be anticipated—frequent attendee: 2 visits per day, mid-level attendee: 5 visits per week, and low-level attendee: 1 visit per week [15,17].

### Data Management

All data will be captured using a dedicated web-based data system accessible only to site research personnel. Following completion of any given data form, data will be uploaded to a secure, password-protected server managed by the sponsor and located in Canada. It will be the Contract Research Organization’s (CRO) responsibility to manage data security. Following project completion, the CRO will lock the data system from further changes and securely transfer data to PneumoWave, where data will be securely stored. Site-specific data sets will also be provided to the SIF. All data will be anonymous, using only study IDs.

### PneumoWave Managed Biosensor Data

As soon as the biosensor chest placement has been carried out, chest movement data will commence being captured. Data from the biosensor will be uploaded securely and automatically to a Data Hub stored in a small container, located within the SIF (Figure 2).

The data storage platform (supplied by Galen Data) complies with HIPAA (Health Insurance Portability and Accountability Act) requirements as set forth in the Galen Cloud HIPAA Compliance Matrix (004-0020), General Data Protection Regulation (GDPR) requirements as set forth in the Galen Cloud GDPR Compliance Matrix (004-0021), and California Consumer Privacy Act (CCPA) requirements. Additionally, Galen Cloud deployed on Amazon Web Services (AWS) is Health Information Trust Alliance (HITRUST) certified.

PneumoWave will review both chest movement data stored within the Galen Cloud and study data, including baseline questionnaire, injecting event, acute event, and satisfaction questionnaire data.

**Figure 2 figure2:**
[figure not shown]
Data management flow. CCPA: California Consumer Privacy Act; CRA: Clinical Research Associate; EDC: Electronic Data Capture; GDPR: General Data Protection Regulation; HIPAA: Health Insurance Portability and Accountability Act; HITRUST: Health Information Trust Alliance; OD: overdose.

### Early Withdrawal

Participants may request to withdraw from the study at any stage for any reason without prejudice. Participants will need to complete an early withdrawal form. Participants may also request deletion of all study data collected about them up until the point of their withdrawal.

### Study Procedure Risks and Benefits

It is understood there may be the occasional loss of a biosensor with the key issue being the potential for a participant to leave the facility prior to removal of the biosensor. While site personnel will aim to minimize this risk, it does remain a factor for device accountability or traceability records. The safety risk relating to a biosensor being taken off-site is assessed to be minimal. Anticipated risks are expected to be very minimal and with a low chance of occurrence. This is a noninterventional, observational study with retrospective analysis of the biosensor data and no protocol-specified procedures impacting the standard of care. Even so, potential study risks include data breaches. However, all electronic data will be anonymous and stored on secure, password-protected devices or servers, and accessible only by approved study personnel. Numerical study IDs will be used in place of participant names. All paper-based consent forms containing participant names will be kept on-site at the SIF following completion and will not be removed from the site. ECG electrodes used in the study are designed to be worn for up to 3 days continuously. The average duration of wear is expected to be less than 1 hour; however, there is a low risk of mild skin irritation.

Given the preliminary, small-scale nature of this research, it is not anticipated that there will be any direct benefits to participants. This work aims to advance the development of future devices that may identify and intervene during opioid overdose; however, such devices may not eventuate for a number of years. The absence of immediate benefit will be outlined to participants during the consent process.

### Safety

The capture of safety events will be solely related to adverse device effects (ADE) and will only be captured for an event relating to the use or wearing of the device. All ADEs and serious ADEs will be recorded by site research personnel and will be assessed for severity (mild, moderate, or severe) by the study team.

All ADEs and serious ADEs will be recorded from the time a participant is enrolled until the participant’s last study visit as per the time periods outlined. Participants who have enrolled but then withdrawn prior to wearing the biosensor for the first time will not have adverse events captured. Only unanticipated effects will be captured as reportable ADEs.

### Analyses

#### Statistical Analysis

For the SIF-determined outcome measures (eg, demographic data) and satisfaction survey, descriptive statistics will be reported using means and SD for continuous data. Absolute numbers and percentages will be reported for categorical data. Any statistical software can be used.

#### Biosensor Analyses

##### Reference Event

Staff-identified events are any event that has required an intervention by staff in the facility. Interventions can range from a simple audio stimulus, up to and including requesting an ambulance to attend. These events include those where overdose may not have occurred, but the response will have been managed in the same way according to the site’s standard operating procedures. These incidences will be recorded as an “acute event.” Where an overdose has been clearly identified using the tools mentioned previously, these incidences will be identified as “overdose event.” The analysis will incorporate both types of “reference” events.

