#### SIF-Determined Outcome Measures

The data that will be collected for each opioid injecting event in the SIF are (1) participant study ID, (2) time or date of client presentation to SIF, (3) substances reported by the participant as intended for injecting (confirmation that opioids are being injected), (4) time of opioid use, and (5) any apnea and prompts to breathe.

The outcome data that will be recorded for any intervention by SIF clinical staff (including acute event response) are (1) precise timing of the first clinical indication of acute event, (2) unique ID number of clinician initially assessing the event to be an opioid overdose, and (3) opioid overdose criteria being met (based on-site specific training materials or opioid overdose reference criteria). These are based on the measures that are described next.

The outcome measures that will be collected for each acute event (including prompts), as applicable are (1) response to audio, physical, and painful stimuli; (2) level of consciousness—timepoints as per standard of care, recorded (using Alert Verbal Pain Unresponsive [AVPU] scale—see Multimedia Appendix 2) at intervals indicated by clinical concern; (3) respiratory rate recorded at least every 5 minutes (though in practice, likely more often) after first clinical indication of opioid overdose; (4) heart rate—timepoints as per standard of care; (5) oxygen saturation via pulse oximetry were measured—timepoints as per standard of care, recorded at intervals indicated by clinical concern; (6) administration of oxygen; (7) administration of manual resuscitation or ventilate (bag-valve-mask ventilation); (8) administration of airway adjunct (nasopharyngeal or oropharyngeal airway); (9) administration of naloxone (yes or no); (10) cardiopulmonary resuscitation; and (11) ambulance called.

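### Acute reference events are defined by staff intervention and recorded through it, and with no timing condition on alarms, signal from the staff response can enter training and be credited as detection

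*Protocol article*

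**What the plan says.** All references are to the protocol article.

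- **Positive label.** Reference Event defines the broad category: "Staff-identified events are any event that has required an intervention by staff in the facility". The threshold is low: "Interventions can range from a simple audio stimulus, up to and including requesting an ambulance to attend". It adds: "These events include those where overdose may not have occurred, but the response will have been managed in the same way". Events clearly identified as overdoses form a second category, and "The analysis will incorporate both types of" reference event. Study Design agrees that an acute event is one that staff attend to and prompt.
- **Negative label.** Under the Visit 1 procedures, a record of no acute event "will also be maintained if the self-injecting visit occurred without any requirement for site personnel intervention". The Visit 2 procedures repeat this.
- **Recording.** PneumoWave Managed Biosensor Data says capture begins once the sensor is on the chest. Tables 1 and 2 place its return after the injecting event. The event record consists of: "Event start time, event stop time, assessment of event, and event outcome, if an applicable acute event occurs".
- **Staff actions.** SIF-Determined Outcome Measures lists, as applicable, physical and painful stimuli, "administration of manual resuscitation or ventilate (bag-valve-mask ventilation"), and CPR.
- **Times collected.** The same section records "precise timing of the first clinical indication of acute event". The visit procedures add the start and end of interventions and, where obtainable, an estimated injection time.
- **Scoring.** Algorithm Under Test compares the algorithm with the reference events on sensitivity and on the rate of false alarms. It states no time by which an alarm must occur. Study Design says the same data serve to test and to develop the signatures.

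**The concern.** The sensor measures chest motion, and several of the listed staff actions move the chest. For acute events, the label coincides with staff having acted. An algorithm refined on whole records could therefore learn features of the response as well as the breathing change that preceded it. An alarm first raised while staff are already acting could also be scored as a success.

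The Introduction gives the purpose as detection when a person may be alone or when the onset goes unnoticed. Nobody is handling the person then, so a signature built partly on handling would not carry over. An alarm that comes only after staff have acted is also weak evidence of early, real-time detection. Sensitivity is one of only two performance measures named, so its meaning matters even in a pilot.

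**Working it through.** **1. Label against staff action.**

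| Record | Staff intervention present? | Basis |
|---|---|---|
| Acute event | Yes, by definition | Reference Event; Study Design |
| Overdose event | Yes, as a subset of staff-identified events, with clinical criteria also met | Reference Event; SIF-Determined Outcome Measures |
| No acute event | No, by definition | Visit 1 and Visit 2 procedures |

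Intervention is thus present in 100% of positives and 0% of negatives. This concerns the label. It does not show that a chest-motion trace of handling exists in every positive.

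**2. Does the record span the intervention?** Capture starts at attachment and the sensor comes back after the injecting event. Nothing shown says it is removed, or the recording cut, when staff respond. Post-intervention signal is therefore available to a retrospective analysis.

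**3. Does the comparison exclude that signal?** Algorithm Under Test sets no window. Primary Outcome Measures contrasts chest motion before and after injection, which is a different cut from before and after staff action.

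**4. The plan's own figure.** The document gives no sensitivity figure to reproduce. The only relevant count is the target of about 40 events from 4000 visits at a 1.2% rate. 4000 × 0.012 = 48, so 40 is not reproduced (40/4000 = 1.0%). That discrepancy is separate and nothing below depends on it. I use 40 as the stated target, with one event per visit.

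**5. Illustration (s and f are assumed; the document gives neither).** Let s be the sensitivity from alarms before the first staff action, and f the share of otherwise missed events credited from later signal.

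Apparent sensitivity = s + (1 − s) × f

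| s | f = 0.25 | f = 0.50 | f = 0.75 |
|---|---|---|---|
| 50% | 62.5% | 75% | 87.5% |
| 70% | 77.5% | 85% | 92.5% |

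For example, 0.50 + 0.50 × 0.50 = 0.75. With 40 events, 20/40 has an exact 95% interval of 34% to 66%, and 30/40 one of 59% to 87%. With the 10 overdoses reported in Results, each event credited late moves sensitivity by 1/10, or 10 percentage points.

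**6. Limiting case.** Suppose handling were visible in every positive. A detector of handling alone would then score 40/40 (95% interval 91% to 100%), with 0 false alarms in 4000 − 40 = 3960 visits (upper limit 0.09%) and no early detection at all. This shows what the stated measures cannot rule out. It is not a forecast.

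**7. Direction.** For a fixed algorithm, whole-record scoring cannot fall below s, because an earlier alarm counts either way. Relative to an unattended person, however, the error can run downward. Added motion may mask a reduced-movement event, prompt action may cut the depression short before an alarm is reached, and mixed signal may blur the trained signature.

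**The case against.** The strongest reply is that the article is a condensed account. Rules for matching alarms to events belong in a full protocol or SAP that is not shown, and the times needed for them are collected. This stands to the extent that a reader might infer that late alarms **will** count as detections or that the recorded times will be ignored. The document says neither. What remains is the stated intervention-based definition joined to a stated comparison that has no timing condition.

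A reader might also infer that every positive record is contaminated. That is not supported. An event can qualify on an audio stimulus alone, which need not move the chest, and ventilation and CPR are recorded only where given. Nor is intervention the whole definition throughout: Primary Outcome Measures describes the positive group by hypoxia and defined criteria, and overdose events need clinical identification.

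A third tempting inference is that sensitivity is overstated. The algorithms look for reduced chest movement, so handling may hide events as well as mimic them. A fixed reduced-movement rule is less exposed to the shortcut, but this algorithm is experimental and is to be refined on these records.

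Finally, scoring every alarm after staff action as a miss would partly measure how fast staff are, and would penalise correct detection of depression still in progress. That objection stands and shapes the fix. The pilot status, with effectiveness testing left to a later study, limits the consequences but does not settle what this study's sensitivity means.

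**Conclusion.** The concern holds in a limited form. The dividing line between acute events and safe visits is staff intervention, the recording continues through it, and the stated comparison sets no timing condition. Signal from the response can therefore enter both training and scoring, and the reported sensitivity may not reflect early detection in an unattended person.

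Neither the size nor, for that intended use, the direction of the effect can be derived from the document. The 50% to 75% example and the limiting case rest on assumed inputs. The conclusion assumes that the sensor stays on and recording during the response, which follows from the attachment and return schedule but is not stated outright. It also assumes that no analysis window is set in a document not shown.

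**What to change.** Amend Reference Event and Algorithm Under Test as follows.

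1. Limit algorithm training to signal before the first staff action, using the recorded intervention start time together with the time of first clinical indication. State which one sets the cut when they differ.
2. Draw comparison windows from safe visits, matched on time since injection where injection time was recorded. Report how many records cannot be matched.
3. Report sensitivity separately for alarms before and after the first staff action, with lead time. Keep later alarms visible rather than scoring them all as misses.
4. Base any claim of real-time or early detection on the pre-intervention figure.
5. Name staff handling as a limitation next to participants' own movement, which the Discussion already mentions.

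The cost is analysis wording and derived windows, with no new data collection; Results says analysis was still ongoing. The downsides are less signal per event, a possibly lower headline sensitivity, and little contribution from events that staff attended promptly. Injection times are estimated from a distance, so the matching will be approximate.
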